### Primary Outcome

#### Open-Road Course Driving Performance Test

Our standardized road course is a fixed route in Gainesville, Florida, with a gradual progression of driving difficulty. The scoring mechanism is based on errors, which are used to evaluate driving maneuvers. A standardized scoring sheet with a total of 49 driving maneuvers and 8 types of possible driving errors is used by the certified driver rehabilitation specialist (CDRS) or driver rehabilitation therapist (DRT) while the participant is driving. The driving errors are defined in the subsequent subsections.

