#### Scoring Criteria

Scoring in this study is based on assessing driving errors to discern how participants perform on the road and to identify driving performance deficits. The 8 driving errors are being measured on a scale from 0 (physical intervention indicating very poor driving performance) to 3 (no driving errors indicating good driving performance). For each maneuver, a maximum score of 3 is given if no errors are committed. Specifically, the scoring is as follows: 3 indicates no errors, 2 indicates any error in any driving behavior for the given maneuver, 1 indicates that the evaluator must use verbal cues or repeat instructions (not hearing-related) to modify or change driving behavior, and 0 indicates that physical intervention (such as grabbing the steering wheel or using the auxiliary brake) is required. At the end of the driving course, the sum of the points attained is computed as the sum of maneuvers score (SMS), ranging from 0 to 147, with 147 indicating a perfect driving score (zero errors) [34,35], which provides detailed information to identify deficits in the participants’ driving performance.

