After sobriety is ascertained, the task continues with a “warm-up” period using a dual-brake program vehicle (a 2019 Toyota Camry or 2020 Toyota Corolla) in a parking lot. The evaluator will review the general controls for mirrors, seats, and automatic transmission shift. Drivers will perform simple maneuvers and practice perpendicular or angled parking for approximately 3 minutes. The course is designed to progress from simple to moderate and then high-complexity environments. The parking lot or “off-road” area transitions directly into a residential or simple driving environment. To ensure adequate exposure within each level of difficulty, the course is designed to include at least 3 examples of each type of maneuver within each level of difficulty. Multimedia Appendix 1 contains road course documentation and scoring details. The assessments will take place during daylight hours from mid-morning through late afternoon—approximately 9 AM to 4 PM. Assessments will be cancelled if the clinical evaluator deems the conditions unsafe due to inclement weather or unsafe road conditions. The complete course consists of 49 maneuvers through Gainesville, Florida. The driving performance form is designed so a single evaluator can document observed driving errors adequately and remain attentive to the driver and surrounding conditions. The fixed route ensures all participants are given the same maneuvers. The evaluator will check observed errors from a list of behaviors under each maneuver. The SMS is the total number of points accumulated over the set number of maneuvers divided by the total possible number of points (49 maneuvers × 3 = 147 possible points, indicating perfect driving). Participants will be compensated US $50 for this assessment and an additional US $20 as a transportation supplement for expenses such as gas or rideshare fees spent traveling to the Smart House.

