### Data Analysis Plan

We will initially compute descriptive statistics to provide demographic and clinical characterization of the study sample. We will examine whether the MMG and NMG participants differ at study entry on potential confounding variables before testing study hypotheses and we will test medical and demographic variables as predictors of study outcomes. Medical and demographic variables that are significant predictors will be used as covariates and controlled for in subsequent analyses. Highly skewed covariates will be analyzed using spline, log transformation, or other acceptable normalization (eg, square root transformation). Finite mixture modeling and generalized linear modeling, accounting for individual- and group-level outcomes, will be used to test the study hypotheses. Primary study hypotheses will be tested using analysis of covariance (ANCOVA), given that the primary outcome SMS is a continuous variable (range 0-147) and inclusion of covariates will reduce error variation and increase statistical power, particularly as this study lacks random assignment.

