## Discussion

### Expected Findings

Our work will (1) focus on medical marijuana use with a sample who has used daily or most days for 12 months or longer, (2) confirm medical marijuana use based on date of card qualification and purchase history—all products used in the previous year will be downloaded from the OMMU to quantify use patterns over the course of the past year, (3) quantify medical marijuana use for 7 days before the on-road driving performance task using twice-daily ecological momentary assessment for all MMG participants, (4) measure prescription opioid using urinalysis on the day of the drive, and (5) measure driving performance using an open-road course under the observation of a CDRS or DRT trained to evaluate impaired driving in a test vehicle with the needed evaluator controls (eg, eye check mirrors and auxiliary brake) to maneuver the car and prevent any adverse occurrences, including near misses or crashes, if any dangerous situations arise. Older adults are more likely to be involved in crashes at intersections or during merges, and these crashes are inherently more fatal [45,46]. The challenging, fast-paced environment presented by intersections and merges puts extra demand on cognitive, sensory, and motor domains critical for driving, and slower response time, inattention, and difficulty with executive functions may lead to more driving errors, potential crashes, or fatal crashes [44]. Therefore, measurement using a standardized open-road course with a clinical CDRS or DRT in the passenger seat of the vehicle will ensure optimal safety of the driver and other road users. Specifically, we will provide state-of-the-art technology (a 2019 Toyota Corolla and a 2020 Toyota Camry, both equipped with instrumentation) for high-impact, low-risk, rigorous measurement of driving to assess users under the influence of medical marijuana and the combined effect of prescription opioid use. As medical marijuana use grows, prescription opioid use continues, and the US population ages, this study provides needed data to develop risk screening, recommendation guidelines, and relevant interventions for this population.

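### The driving score depends on one evaluator and one of two cars, and the article states neither a rule balancing them across groups nor a guaranteed place for them in the model

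*Protocol article*

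**What the plan says.** **Scoring.** Under Open-Road Course Driving Performance Test, the standardized sheet "is used by the certified driver rehabilitation specialist (CDRS) or driver rehabilitation therapist (DRT) while the participant is driving". Under Assessment Session 2, "The driving performance form is designed so a single evaluator can document observed driving errors adequately". No second rating is described. Data Blinding refers to more than one such evaluator and says they are blinded to group.

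**Judgment.** Gap Acceptance Errors are called on the evaluator's judgment. Under Scoring Criteria, "1 indicates that the evaluator must use verbal cues or repeat instructions (not hearing-related) to modify or change driving behavior", and a 0 means that the evaluator intervened physically. The two lowest scores therefore depend partly on when the evaluator decides to act.

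**Cars.** Assessment Session 2 describes the drive as "using a dual-brake program vehicle (a 2019 Toyota Camry or 2020 Toyota Corolla) in a parking lot", and Mitigation of Risk names the same pair. Expected Findings instead gives "a 2019 Toyota Corolla and a 2020 Toyota Camry, both equipped with instrumentation", with the model years exchanged.

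**Balance and analysis.** Participants lists race and sex as matching factors and age as a balancing factor. Hypothesis 1a and 1b starts with an unadjusted two-sample t test, followed by an ANCOVA on sociodemographic, driving, behavioral and clinical variables that prove significant. The general rule in the Data Analysis Plan is: "Medical and demographic variables that are significant predictors will be used as covariates and controlled for in subsequent analyses". Evaluator and car are named in none of these places.

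**The concern.** Groups are not randomized, so nothing in the design makes the mix of evaluators or cars equal by default. If a stricter evaluator happens to score a larger share of MMG drives, the MMG mean falls with no true difference. If a more lenient one does, a real difference is hidden. Blinding stops an evaluator from scoring the two groups differently. It does not equalize a strict and a lenient evaluator who see different proportions of the groups.

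The stated analysis does not close the gap. The t test cannot adjust for anything. Entry into the ANCOVA depends on a significance test, and an imbalanced factor can shift the group contrast while its own test falls short of significance. At stake is whether a modest difference in SMS can be attributed to marijuana exposure.

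**Working it through.** **The plan's own figures.** The article gives no evaluator variance, inter-rater reliability or SD for SMS, so there is no stated figure to reproduce on this point. The sample size serves only to settle the significance level. The total of 198 (f = 0.20, 80% power) is reproduced by a noncentral F calculation with α = 0.05 and 1 numerator df: N = 199, with power 0.80 at 198. With the printed α of 0.5 and 1 df the answer would be 54. I therefore use two-sided 0.05.

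**Inputs**
- 125 per group (Sample Size and Power).
- Severity gap s between two evaluators, in SD units: assumed, 0.2 to 0.5.
- Imbalance p, the difference between groups in the share of drives scored by the stricter evaluator: assumed, 0 to 40 points.

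**Formulas**
- Bias = s × p.
- SE of the group difference = √(2/125) = 0.126 SD.
- Type I error = P(|Z + bias/SE| > 1.96).

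| s (SD) | p | Bias (SD) | Bias/SE | Type I error |
|---|---|---|---|---|
| any | 0 | 0 | 0 | 5.0% |
| 0.2 | 0.10 | 0.02 | 0.16 | 5.3% |
| 0.3 | 0.20 | 0.06 | 0.47 | 7.6% |
| 0.5 | 0.20 | 0.10 | 0.79 | 12.4% |
| 0.5 | 0.40 | 0.20 | 1.58 | 35.3% |

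The same arithmetic applies to a car effect of size s.

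**Scale.** The effect f = 0.20 (d = 2f = 0.40) belongs to the aim 2 subgroups. For aim 1, which is the contrast above, the article expects a medium effect. Taking d = 0.5 as the conventional medium value (an assumption), a bias of 0.10 SD is 20% of it and 0.20 SD is 40%.

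**Precision only.** If assignment is unrelated to group and two evaluators share drives equally, the added variance is s²/4. For s = 0.5 that is 0.0625, so the SE rises by √1.0625 = 1.03, about 3%. For s = 0.2 it is 0.01, about 0.5%.

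**Could assignment be linked to group?** Drives run from about 9 AM to 4 PM, and MMG drives alone must fall 8 to 12 hours after last use. A drive at noon then implies last use between midnight and 4 AM, while last use at 10 PM implies a drive no later than 10 AM. Evening users would tend toward morning slots, whereas NMG participants face no such limit. If evaluators or cars vary by shift, their shares would differ by group. The groups also come from different recruitment streams, and recruitment is expected to run from 2025 to 2029, long enough for staff to change. This gives a route to imbalance. It is not evidence of one.

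**The case against.** The strongest reply is that much of this rests on silence. The article condenses a fuller protocol, and evaluator assignment, calibration and car scheduling may be set out there. A reader might infer that evaluator and car are in fact unbalanced and left out of the model. The documents do not support that: no section says they are unbalanced, and the Hypothesis 1a and 1b rule admits driving variables, which could be read to include them. Nor does any section say that control drives come later than MMG drives, or that the score sheet already records evaluator and car.

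There are also real safeguards: blinding, a standardized form with anchored scores, a fixed route, trained evaluators, a vehicle warm-up, and a measure described as valid and reliable. No figure in the article suggests that either sedan changes SMS, and the larger biases in the table need upper-range assumptions.

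All of that stands, and it limits the claim. It does not remove the point, because the article does state its analysis rule. Even on the generous reading of driving variables, entry still depends on significance, and the first test is unadjusted. The safeguards standardize the task and keep scoring independent of group, but they do not equalize evaluators' thresholds.

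**Conclusion.** The point holds as a gap in protection, not as a demonstrated bias. As stated, the plan has no rule balancing evaluator or car across groups and no guarantee that either is in the model. Bias arises only if assignment is associated with group. In that case it is 0.02 to 0.20 SD over the assumed range, with type I error from about 5.3% to 35%. Otherwise type I error stays at 5% and the loss is a small amount of precision. Every severity gap and imbalance used here is an assumption. A cheap improvement is available and worth making. The exchanged model years are a clerical inconsistency and carry no weight in the confounding argument.

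**What to change.** 1. Record evaluator and car for every drive, and recover both for drives already done. Only 30 of the planned 250 participants were enrolled as of November 2025.
2. Schedule so that each evaluator and each car sees similar numbers of MMG and NMG participants throughout recruitment, keeping both the same within a race-sex match where feasible. A fixed term can separate evaluator from group only if each evaluator sees both groups.
3. Include evaluator, and car, as fixed terms in the primary ANCOVA regardless of significance.
4. Separately, reconcile the cars named under Assessment Session 2 and Mitigation of Risk ("a 2019 Toyota Camry or 2020 Toyota Corolla") with those under Expected Findings ("a 2019 Toyota Corolla and a 2020 Toyota Camry").

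**Cost.** Scheduling becomes less flexible, and strict within-match assignment may be hard to hold through staff changes up to 2029, hence the words where feasible. The model loses a few degrees of freedom. At N = 250, f = 0.20 and a 1-df test, power is 0.883 whether 2 or 4 parameters are fitted, so that loss is negligible.

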#### Assessment Session 3 (Qualitative interview)

Participants will be a convenience sample recruited from the MMG and NMG after AS2. We anticipate that 60 participants (30 per group) will be adequate to reach qualitative saturation [41], and interviews will continue until saturation is reached. We will ensure that groups are balanced by age, race, and sex to ensure the breadth of perspectives from both sides. Interviews will be one-on-one, semistructured, and conducted using an interview guide; sessions will be audio recorded and transcribed using a HIPAA-compliant research transcription company. The goal of this aim is to understand self-regulation of use, including types of products used, THC/cannabidiol percentages, and quantity of use, by integrating qualitative findings and quantitative data to identify markers for risk screening, use guidelines, and intervention targets for this population. Participants will be compensated US $50 for completing the qualitative interview. Participants may receive up to US $245 if all assessments are completed as directed in the study protocol.

### Study Conditions

#### Exposure: Medical Marijuana Group

Any patient who has been certified for medical marijuana use and has held an active medical marijuana card in the state of Florida for at least 12 months, is aged 50 years or older, endorses chronic or severe pain, and reports using medical marijuana purchased through the state of Florida dispensation system daily or most days of the week for the past year, as documented by purchases over the course of the year in the OMMU database, has an active Florida driver’s license and the visual acuity to perform the task with or without vision corrective apparatus (glasses or contacts). Medical marijuana was legalized in Florida in January 2017. Per Florida state statute 381.986, residents of Florida have access to marijuana for medical use if authorized by a qualified medical marijuana physician. All medical marijuana patients must register with the state for access to medical marijuana, which includes the certification process identifying a qualifying condition, the reason the patient is authorized to use medical marijuana, and tracking all purchases through the OMMU. Qualified medical marijuana patients are allowed to purchase up to 2.5 ounces of smokable flower every 35 days, and limits on the milligrams of all other routes of administration are set by the physician. Patients must be recertified to use medical marijuana every 210 days (7 months). We will track dosage, frequency, type of product used (high vs low cannabidiol/THC), and route of administration. All medical marijuana participants will be recruited from the MMTC, our medical marijuana recruitment partner. Participants will be allowed to complete the drive regardless of a negative or positive urine screen for opioid use. Our current data suggests that approximately 40% of medical marijuana patients will also test positive for opioid use.

#### No Marijuana Use Group (Past 10 Years)

NMG participants will be race-sex–matched adults aged 50 years and older who endorse chronic or severe pain, recruited from the community using flyers and handouts, newspaper advertisements, internet advertisements, social media, in-person lectures and events, and contact by mail, email, and the infrastructure and support of Oak Hammock at the UF—a residential retirement community. We will also phone individuals enrolled in the UF Clinical and Translational Science Institute’s Integrated Data Repository, a database organizing clinical information across UF Health’s clinical and research programs [42]. Individuals enrolled in UF Health services or taking part in UF research studies can provide consent to be contacted within this system, and data can be queried using National Institutes of Health’s Informatics for Integrating Biology and the Bedside tool, which provides researchers with a HIPAA-compliant and UF Institutional Review Board–approved limited dataset [43]. In querying this dataset for adults aged 55-84 years (adults aged 45-54 years were grouped together and thus excluded from the query) with who endorse chronic or severe nonmalignant pain, the tool reported 7463 potential participants who have consented to be contacted for research participation. Participants will be allowed to complete the drive regardless of a negative or positive urine screen for opioid use. Our current data suggests that approximately 25% of control participants will also test positive for opioid use, with literature estimating of up to 50% of patients with chronic or severe nonmalignant pain using opioids.

#### Data Blinding

Due to the extent of participant engagement with the CDRS and DRT, we will ensure that the CDRS and CDRT, who are responsible for the primary outcome, are blinded to participant condition to minimize any potential bias.

### Participant Data Protection

Any computers or tablets containing identifying data, such as participant logs, will be protected by multiple security codes using standards set by Florida State University. During data analysis, all identifying information, except the participant identification number, will be removed. The Intervention Research Advancing Care Excellence laboratory (director: NE) and Institute for Driving, Activity, Participation, and Technology (director: SC) benefit from outstanding security, backup, and technical support provided by the University of Florida Clinical and Translational Research Institute and the College of Public Health and Health Professions. Data are collected at the UF Smart House and are managed by our central data management team. All electronic medical records marijuana data will only be accessed by core study staff with the appropriate training and prior institutional review board approval.

### Safety Monitoring

#### Primary Outcome

The safety of all participants will be ensured through: (1) sobriety testing, (2) vision screening, (3) no drives conducted in rainy conditions, (4) all drives completed during daylight hours during and periods of lower traffic congestion, and (5) use of a dual-brake controlled vehicle equipped with an eye check mirror for the CDRS or DRT. In addition, a closed-road driving observation period will be conducted by the CDRS or DRT, during which any safety concerns will result in termination before entering the open road. The CDRS or DRT will provide verbal cues as needed and take over steering if necessary to prevent harm, as trained and in accordance with best practices.

#### Mitigation of Risk

Our on-road course is highly regulated. The CDRS or DRT will observe for safety, provide instructions to the driver, and implement interventions such as braking the vehicle or taking over steering if necessary. No drives will be conducted in moderate to heavy rainy conditions (as determined by the CDRS or DRT), and all drives will be completed during daylight hours and midday during periods of lower traffic congestion. During the AS2 drive study visit, we will check participants’ visual acuity and motor skills. After those steps, we will teach participants about the vehicle they will drive—a 2019 Toyota Camry or a 2020 Toyota Corolla dual-brake vehicle with in-vehicle information systems (eg, a back-up camera) and advanced driver assistance (eg, emergency braking control) features—and make sure they know how to operate the vehicle’s controls (eg, steering, brake, gas). None of the other smart features (eg, adaptive cruise control or lane centering system) will be activated during the drive.

### Data Analysis Plan

We will initially compute descriptive statistics to provide demographic and clinical characterization of the study sample. We will examine whether the MMG and NMG participants differ at study entry on potential confounding variables before testing study hypotheses and we will test medical and demographic variables as predictors of study outcomes. Medical and demographic variables that are significant predictors will be used as covariates and controlled for in subsequent analyses. Highly skewed covariates will be analyzed using spline, log transformation, or other acceptable normalization (eg, square root transformation). Finite mixture modeling and generalized linear modeling, accounting for individual- and group-level outcomes, will be used to test the study hypotheses. Primary study hypotheses will be tested using analysis of covariance (ANCOVA), given that the primary outcome SMS is a continuous variable (range 0-147) and inclusion of covariates will reduce error variation and increase statistical power, particularly as this study lacks random assignment.

### Hypotheses Testing

#### Hypothesis 1a and 1b (Driving Performance—Between-Group Analyses)

To answer the question of whether long-term medical marijuana use affects behavioral driving outcomes, we will compare the SMS between MMG and NMG using an independent 2-sample *t* test. ANCOVA will then be used to determine whether the two groups differ on SMS by adjusting for significant sociodemographic, driving, behavioral, and clinical variables. A model-building approach, which will include age, will be used, and analyses will be performed with and without covariate adjustment, since sample-dependent variables may explain some outcome variance. Tukey’s honestly significant difference test or Tukey-Kramer test will be used to estimate the clinical significance of the findings.

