### Study Design

We are using a two-group observational study design with a group with medical marijuana use for more than 12 months daily or most days of the week (medical marijuana group [MMG]) versus a race-sex–matched group with no marijuana exposure in the past 10 years and no history of daily use (no marijuana group [NMG]). We chose 10 years as the no–marijuana-exposure window to ensure that recreational use was not a confounder. We will test the difference between long-term medical marijuana exposure and no marijuana exposure on driving performance outcomes in adults aged 50 years and older who endorse chronic or severe nonmalignant pain through an open-road driving assessment. There will be up to 3 in-person assessment sessions over approximately 10 days. Assessment session 1 (AS1; the first assessment session) is the onboarding session, which will include informed consent, sociodemographics, a battery of psychosocial measures, and urinalysis to test for the presence of marijuana, opioids, and other commonly misused substances. After AS1, we will use ecological momentary assessment to capture medical marijuana use (MMG) or mood and medication use (NMG). MMG participants will complete twice-daily assessments of medical marijuana use for 7 days. To attention match, the NMG will complete twice-daily assessments of mood and any medication use daily for 7 days. Assessment session 2 (AS2; the second assessment session), the open-road driving performance task, will occur approximately 8 days after AS1 and, for MMG participants, 8-12 hours after the last medical marijuana use. At AS2, vision screening to ensure appropriate visual acuity and urinalysis will be completed before the drive. Additionally, we will request permission from MMG participants only to extract Office of Medical Marijuana Use (OMMU) purchase history data, which include the dispensary name, date of purchase, quantity of medical marijuana purchased, and route of administration. Assessment session 3 (AS3; the third and final assessment session) will be a qualitative interview with a subset of participants (n=60) regarding self-regulation of medical marijuana and prescription medication use, to be completed no later than 3 days after the drive (Figure 1).

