### Participants

Participants will include 250 adults aged 50 years and older who have been registered with the state of Florida for at least 12 months to obtain medical marijuana and report use daily or most days of the week (n=125), as well as race-sex–matched participants with no marijuana use in the past 10 years and no history of daily use (n=125). Textbox 1 provides the inclusion and exclusion criteria. To examine age as an independent factor, we will ensure that age variability is balanced between the two groups. We selected a 10-year no marijuana exposure window to ensure that recreational use does not confound our findings. We chose to match participants by sex to ensure that sex differences do not account for driving performance outcomes. We also chose to match participants by race to ensure that differences in psychomotor functioning by race among older adults do not account for the findings. Groups will be balanced by age (±1 year) to allow for observation of group differences by age.

Inclusion and exclusion criteria.

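### Race and sex are matching factors, yet hypothesis 1 starts with an unadjusted t test and no SMS model is guaranteed to keep them

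*Protocol article*

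**What the plan says.** **Design.** Study Design compares medical marijuana users "versus a race-sex–matched group with no marijuana exposure in the past 10 years". Participants gives the reason for one factor: "We chose to match participants by sex to ensure that sex differences do not account for driving performance outcomes". It gives a similar reason for race, and adds: "Groups will be balanced by age (±1 year) to allow for observation of group differences by age".

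**Analysis.** Data Analysis Plan states: "Primary study hypotheses will be tested using analysis of covariance (ANCOVA". Its general covariate rule is: "Medical and demographic variables that are significant predictors will be used as covariates and controlled for in subsequent analyses". The hypothesis 1 section nevertheless opens with the comparison "we will compare the SMS between MMG and NMG using an independent 2-sample" *t* test. ANCOVA comes second, "adjusting for significant sociodemographic, driving, behavioral, and clinical variables". Age is named as part of the model building; race and sex are not. Results are to be given with and without adjustment.

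**Aim 2.** Hypothesis 2a repeats the pattern for opioid users against non-users: an unadjusted two-sample t test, then ANCOVA with variables chosen by significance and adjusted R². Hypothesis 2b reuses the best model from aim 1 within each marijuana group.

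No section mentions a paired analysis or a matched-set term. Mixed models appear only under Alternative Design Plan, as a fallback if ANCOVA's assumptions fail.

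**The concern.** Factors chosen for matching because they may drive the outcome belong in the analysis model. An unadjusted t test leaves their variance in the error term, although matching has already removed their contribution to the difference between groups. Its standard error therefore overstates the true uncertainty. A significance rule then leaves it to the sample whether race and sex enter the ANCOVA.

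Three things are at stake: some precision in the t test; protection against imbalance if matching does not survive to the analysed sample; and basic adjustment in the opioid comparison, where the design balances nothing.

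**Working it through.** **Inputs from the article (Sample Size and Power).** f = 0.20, power 80%, N = 198, 125 per group planned, 5% early termination. For two equal groups d = 2f = 0.40. Evaluable per group: 125 × 0.95 = 118.75, taken as 119.

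**Assumptions.** Two-sided alpha of 0.05 (the article prints 0.5). The share of SMS variance explained by age, sex and race together is not given; I use R² = 0.10 to 0.25.

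**Reproducing the article's figure.** Noncentral F with λ = f²N and 1 numerator df, alpha 0.05: power at N = 198 is 0.7997, and 199 reaches 80%. The two-mean formula at d = 0.40 gives 99 per group, 198 in total. So d = 0.40 is the effect behind the stated 198. The article expects a larger effect for aim 1, so 0.40 is cautious here.

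**Step 1, t test standard error.** Excess = 1/√(1 − R²) − 1.
- R² = 0.10: 1/0.949 − 1 = 5.4%
- R² = 0.25: 1/0.866 − 1 = 15.5%

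**Step 2, power.** Noncentral t, 236 df, noncentrality d/√(1 − R²) × √(119/2).

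| Analysis | Noncentrality | Power |
|---|---|---|
| Unadjusted | 3.085 | 0.867 |
| Adjusted, R² = 0.10 | 3.252 | 0.900 |
| Adjusted, R² = 0.25 | 3.563 | 0.944 |

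The gaps are about 3 and 8 points. The unadjusted row gives the t test no credit for matching. Under intact matching its power is approximately Φ((3.085 − 1.970)/√(1 − R²)): 0.880 at R² = 0.10 and 0.901 at 0.25. The gaps then shrink to about 2 and 4 points.

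**Step 3, direction.** Under intact matching the t test's type I error is approximately 2Φ(−1.970/√(1 − R²)): 0.038 at R² = 0.10 and 0.023 at 0.25. Both lie below 0.05.

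**Step 4, ANCOVA: forced versus selected.** Simulation of 4,000 trials per setting, 125 per group, exactly matched on two binary factors, retention at p < 0.05. Mean standard errors with no true difference:

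| R² (race + sex) | t test | Forced in | Kept if significant |
|---|---|---|---|
| 0.02 | 0.1263 | 0.1250 | 0.1252 |
| 0.10 | 0.1263 | 0.1198 | 0.1198 |
| 0.20 | 0.1263 | 0.1130 | 0.1130 |

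Selection costs almost no precision, because a factor is dropped mainly when it explains little.

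**Step 5, how often a weak factor drops out.** With 238 evaluable and retention at p < 0.05 (the threshold is assumed), a factor explaining 1% of variance has noncentrality √(238 × 0.01/0.99) = 1.55 and is dropped about 66% of the time. At 2%, √(238 × 0.02/0.98) = 2.20, and it is dropped about 41% of the time. Under intact matching this is harmless; without matching, whether the factor is adjusted for depends on the sample.

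**Step 6, where matching does not protect.** The article plans for drives not completed, including because of intoxication, and a failed sobriety test ends the visit before the drive. These losses come after entry and may differ between groups. In aim 2 the opioid contrast was never matched. The documents give no figures from which to size either bias.

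**The case against.** The strongest reply is that the t test does not decide anything. Data Analysis Plan names ANCOVA as the test of the primary hypotheses, expressly to reduce error variance in a non-randomised study, and age is already in it. Step 4 shows that the significance rule costs almost nothing in precision while matching holds. On the article's own planning effect, even the unadjusted test has about 87% power. The plan also compares the groups on potential confounders at entry, and Missing Data promises sensitivity analyses with adjustment for variables related to systematic missingness. All of this stands, and it rules out four stronger readings that a reader might infer:

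- *That the error bars ignore the design throughout.* This is true of the t test, not in any material way of the ANCOVA under intact matching.
- *That false positives are inflated.* Step 3 shows the opposite.
- *That a paired analysis is required.* The article speaks of matched and balanced groups, which is compatible with frequency matching; it never states one-to-one pairs.
- *That aim 1 is seriously underpowered.* Power of 63% for the t test needs d = 0.30, which appears nowhere in the article. The gains in Step 2 also include age, which the ANCOVA already names.

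The reply does not cover two things. The check at study entry cannot detect imbalance that arises from later losses, and the missing-data provision is a secondary analysis. Neither gives race and sex a fixed place in the aim 2 models.

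**Conclusion.** The point holds in limited form. The plan matches on race and sex as possible causes of driving differences, then leads with a test that ignores them and makes their place in the ANCOVA conditional on significance.

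For the t test the standard error is about 5% to 15% too large, and the power cost is at most about 3 to 8 points. Both ranges assume R² of 0.10 to 0.25, and the power figures also assume d = 0.40 with 119 per group. The error is conservative. For the primary ANCOVA with matching intact, the precision loss is negligible. The case for change therefore rests on robustness to early terminations and on the unmatched opioid comparison; neither bias is quantified. This is an inexpensive improvement to a stated rule, not a flaw that invalidates aim 1.

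**What to change.** 1. Keep sex, race and continuous age in every SMS model for aims 1 and 2, regardless of significance. Apply any selection rule only to further covariates.
2. In the hypothesis 1 section, state that this ANCOVA is the test of the hypothesis, in line with Data Analysis Plan, and report the independent t test as descriptive only.
3. State whether matching is one-to-one or by frequency. Add a matched-pair term only if individual pairs are actually formed and recorded.

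The cost is wording: race, sex and age are already collected for matching and balancing. In aim 2 the change removes confounding by these three factors only, to the extent the model captures their effects.
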